### Measuring instruments

#### Primary clinical outcome measures

The primary outcome variables are 1) the frequency and severity of behavioural problems of the person with dementia as assessed by the Neuropsychiatric Inventory (NPI) [37] and 2) psychological stress of the primary informal caregiver as measured by the General Health Questionnaire (GHQ-12) [38]. The NPI includes 12 domains which measure severity (3-point scale) and frequency (4-point scale) of behavioural and psychological symptoms of the patients as well as the emotional impact of the symptoms on the caregivers. Analyses of the psychometric properties of the original ten-item version showed high internal consistency reliability for the frequency*severity product scores (Cronbach’s α = 0.88) and for the specific severity (α = 0.87) and frequency (α = 0.88) ratings [37,39]. The NPI was chosen as the primary outcome in this study because behavioural problems often precede the more relevant cost-carriers like crisis management or institutionalization [40-43] and case management is expected to positively impact behavioural problems and the stress informal caregivers experience. The GHQ-12 was chosen as a primary outcome measure because it is a general measure of mental health and mental health complaints of the caregiver being an important predictor of institutionalization for the person with dementia [40]. The GHQ-12 comprises of three domains: social dysfunction, anxiety and loss of confidence [44]. The scoring method is a four-point response method with excellent reliability (Cronbach’s alpha = 0.90) [44]. Table 2 presents an overview of the primary and secondary clinical outcomes measures for the persons with dementia and their caregivers.

**Table 2 T2:** Outcome measures in the COMPAS study

**Patient**		**Concept**	**baseline**	**6 months**	**12 months**	**18 months**	**24 months**
Primary outcomes	Neuropsychiatric inventory [37]	Behavioural and psychological symptoms *	X	X	X	X	X
Secondary outcomes	Quality of Life in Alzheimer’s Disease [45]	Quality of Life**	X	X	X	X	X
	Short Form-12 [46]	Health related Quality of Life*	X	X	X	X	X
	EuroQol- 5D + C [47]	Health Related Quality of Life**	X	X	X	X	X
	Camberwell assessment of needs for the elderly (CANE) [21,48]	Needs**	X	X	X	X	X
Cost outcomes	Cost diary	Economic evaluation	X	X	X	X	X
	Time between diagnosis and institutionalization	Economic evaluation	X	X	X	X	X
	Time between first symptoms and institutionalization	Economic evaluation	X	X	X	X	X
Effect modifiers or confounders	Age		X				
	Gender		X				
	Marital status		X				
	Living accommodation	Living alone or with someone	X				
	Education		X				
	Mini Mental State Exam [49]	Cognition	X		X		X
	KATZ Activities of Daily Living-5 [50]	Activities of daily living*	X	X	X	X	X
	Co-morbidity		X				
	Dementia type		X				
	Time in case management		X				
Caregiver							
Primary outcomes	General Health Questionnaire −12 [38]	Emotional stress mental health complaints	X	X	X	X	X
Secondary outcomes	Short Sense of Competence Questionnaire SSCQ [51]	Perceived care competence	X	X	X	X	X
	Pearlin Mastery Scale [52]	Self-efficacy	X	X	X	X	X
	EuroQol 5D[53]	Health related quality of life	X	X	X	X	X
	Carer-Qol [54]	Health related quality of life	X	X	X	X	X
	SF12 [46]	Health related quality of life	X	X	X	X	X
Cost outcomes	Informal care	Economics evaluation	X	X	X	X	X
Quality of care	Quality indicators [43,55]	Process of Care	X	X	X	X	X
Effect modifiers or confounders	Age		X				
	Education		X				
	Relation to person with dementia		X				

*by proxy, **patient and proxy.

#### Secondary clinical outcomes

Secondary outcome variables for the patient include the following. First, Mortality and institutionalization data will be collected from the informal caregiver or general practitioner. Generic Quality of life will be measured by the SF-12 [46] and the EQ-6D (EuroQol) [55]. Next to that, disease specific quality of life will be measured using the Qol-AD (Quality of life in Alzheimer’s Disease) [45] and EuroQoL-6D all quality of life questionnaires will be completed/administered to the care receiver as well as the primary caregiver proxy. Number of met and unmet needs based on the Camberwell assessment of needs for the elderly (CANE) [21,48] administered to the care receiver as well as the primary caregiver proxy. Number of crises defined by emergency department visits, unplanned hospitalization and unplanned institutionalization through the cost diary.

Secondary outcomes variables for the informal caregiver include:

(1) Sense of competence to care measured by the Short Sense of Competence Questionnaire (SSCQ)(Cronbach’s α = 0.76) [51]

(2) Empowerment measured by the Pearlin Mastery scale [52].

(3) Quality of life measured by the Short Form 12, CarerQol [54] and EuroQoL-5D [53].

(4) Number of experienced crises defined by emergency department visits, unplanned hospitalization and unplanned institutionalization.

### Quality of care outcome measures

Quality of care at the micro level of the care receivers is measured by:

(1) 12 indicators on treatment, education, support, and safety (translated and back-translated) from Vickrey asked to the informal caregiver, such as care plan developed, behavioural problems discussed, and non-pharmacological treatments [43];

(2) 10 Indicators from the problems and needs questionnaire, developed by the Dutch Alzheimer Association in conjunction with the Netherlands Institute for Primary Care Research (NIVEL), asked to the informal caregivers [27].

### Cost outcome measures

Cost diaries are used to collect data on use of care and support and direct and indirect healthcare and non-healthcare costs for patients and caregivers to estimate costs from a societal perspective. Direct healthcare costs include formal care such as general practitioner visits and medication use. Direct nonhealthcare costs consist of time spent to care by informal carers. Indirect health care costs include medical costs in life years gained. Indirect non-healthcare costs include days absent from paid work or unable to do daily activities such as housekeeping or voluntary work for caregivers.

### Process outcome measures

For the qualitative process evaluation, the semi-structured interviews with key figures regarding facilitators and barriers of implementation of case management will be based on the theoretical model of adaptive implementation [56,57]. This model distinguishes different phases of implementation (preparation-, implementation- and continuation phase), and describes factors that can influence implementation at the micro- (care-provider, patient and informal carer), meso- (collaboration between care providers/organizations) and macro-level (legal and financial framework) for each phase. The interviews are conducted with case managers, project leaders, care coordinators as well as insurers, client organisations and municipalities until a saturation point is reached. An extensive description of the different case management approaches will be made through data collected by a questionnaire that is based on the Chronic Care model and the essential components of case management as described by Verkade et al. [58].

### Sample size

The sample sizes for the controlled cohort study are calculated based on the primary outcome measures NPI [37] and the GHQ-12 [38]. Based on Callahan et al. [42], who investigated the effect of collaborative care, the estimated change between baseline and follow-up after 12 months on the NPI was −2.5 (SD 13.7) in the intervention group and 2.7 (SD 20.3) in the control group, resulting in a difference of −5.2. The standard deviations reported are the averages for the two time points. Standard deviations of baseline and follow-up scores were assumed equal when calculating the required sample size. The NPI has moderate to high test - retest reliability scores therefore we assumed a within-subject correlation of 0.5 to estimate the standard deviation for the difference scores based on the standard deviations of the baseline and follow-up [11]. A sample size of 140 participants per group is considered sufficient (80% power) to detect a difference of 5.2 in change scores between the groups. This calculation was based on a two group Satterthwaite *t*-test at a one sided significance of α = 0.05. To allow for a drop-out rate of 20% (including patients who withdraw or die in the course of the study), 175 (140/0.80 = 175) participants per group will be recruited.

Based on a study by Dias et al., the difference in GHQ baseline and follow-up at six months was −1.4 (SD 2.8) for the caregiver intervention group and 0.8 (SD 3.4) in the control group [59]. The GHQ has moderate to high test-retest reliability scores. A within-subject correlation of 0.6 when estimating the standard deviation of the difference scores was used. Using a two group Satterthwaite *t*-test with a onesided significance level of α = 0.05, an initial sample size of 21 in each group was estimated to have 80% power to detect a difference in means of −2.2 on the GHQ. A dropout rate for caregivers was assumed at 20% which resulted in a final sample size of at least 26 caregivers per group [59].

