## Background

Dementia is a chronically and devastating disease marked by memory loss and other cognitive impairments as well as behavioural lapses resulting in pronounced consequences for the people with dementia, their families and society. The cost of care for dementia patients, living at home or in a nursing home/home for the elderly, comprised 4.7% (€3.2 billion) of the total health care expenses in 2005 making it one of the most costly diseases in the Netherlands [1,2]. The number of people with dementia is expected to steadily rise due to an ageing population. In the World Alzheimer Report 2009, Alzheimer Disease International estimated that 36 million people worldwide live with dementia, with numbers doubling every 20 years to 66 million by 2030, and 115 million by 2050 [2,3]. The total mean duration of the disease from diagnosis until death was estimated in a large Dutch, prospective, observational analysis of a dementia nursing home cohort to be seven years [4]. Study participants lived in the community for on average five years and then in a nursing home for two years. The median life expectancy from the start of the dementia symptoms varied from 10.7 years for the 65–69 year olds to 3.8 years for those over 90 years old [3]. In a British, population-based cohort of 1304 elderly participants the estimated median survival time from dementia onset to death was 4.1 years for men and 4.6 year for women [5].

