Reviews and meta-analyses of case management have yielded inconsistent results on clinical outcomes such as caregiver burden and depression and on economic outcomes [28-31]. Furthermore, only short term effects on caregiver satisfaction were found [32]. Only one meta-analysis including 15 studies found that risk of institutionalization of dementia patients was reduced by multicomponent interventions aimed at caregivers [28]. Based on this meta-analysis, clinicians are advised to tailor interventions according to the specific needs of the individual caregivers and care receivers [28]. Several reviews have indicated that further research should distinguish subpopulations that could benefit from case management [28-30].

In the Netherlands, patients and caregivers are highly satisfied with case management [33]. However, various models of case management are implemented, differing with respect to how services are delivered and by whom, the training provided to its staff and the means of financing. It is unknown whether there are also differences in clinical and cost-effectiveness between these case management models compared with usual care. In the COMPAS study, two different case management models are studied, that is the linkage model and the intensive case management/joint agency model. These models will be compared with usual care and with each other (description in Table 1). These case managements models were chosen based on their emerging prominence in Dutch healthcare for a number of years. The objective of this study is to identify differences in clinical, process and cost outcomes for people with dementia and informal caregivers between the two case management models and the usual care model. Furthermore, the aim is to identify facilitators and barriers in the implementation of the two case management models. This process evaluation focusses on which aspects are successful and their pitfalls.

**Table 1 T1:** Comparison of case management models and care as usual

**Characteristics of different models**	**Linkage Model**	**Intensive Case management/joint agency model**	**Care as usual**
Central point for registration of cognitively impaired	New clients are referred by GP or health specialist to the central registration point	New clients are referred by GP or health specialist to the Multidisciplinary team at central registration point	No
Delivery of services	Independent services and networks	Mainly offered by one organization	Various networks

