### Data analyses

Demographic, clinical and prognostic characteristics of the study participants will be collected and described in detail. The number of participants with missing data for each variable of interest will be provided along with an analysis to check for selective missingness. Average follow up time will be determined for each model. Reports on adjusted and unadjusted values with confounders will be presented along with 95 percent confidence intervals. Confounders that change beta coefficients more than 10% will be reported.

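### The 80% power for the NPI belongs to a one-sided 5% test; against the 95% intervals the plan reports it is about 71%, and the 20% loss is not tied to the 12-month contrast it supports

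*Protocol article*

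**What the plan says.** The Sample size section takes the NPI effect from a cited collaborative-care trial: a mean 12-month change of −2.5 (SD 13.7) with intervention and +2.7 (SD 20.3) in controls, a difference of 5.2 points. It explains that "The standard deviations reported are the averages for the two time points", assumes equal SDs at baseline and follow-up, and uses a within-subject correlation of 0.5 to obtain the SD of change. The test is a Satterthwaite t-test "at a one sided significance of α = 0.05". The result is: "A sample size of 140 participants per group is considered sufficient (80% power) to detect a difference of 5.2 in change scores".

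The allowance for loss follows: "To allow for a drop-out rate of 20% (including patients who withdraw or die in the course of the study"), which raises 140 to 175 recruited per group. Under Mixed method study design, follow-up is two years with six-monthly assessments.

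On reporting, the Data analyses section says: "Reports on adjusted and unadjusted values with confounders will be presented along with 95 percent confidence intervals". Neither that section nor Effect evaluation or Economic evaluation mentions a one-sided test, a one-sided bound or a 90% interval.

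**The concern.** Two elements of the sample-size paragraph do not match the rest of the article.

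**Sidedness.** A one-sided 5% test corresponds to a 90% two-sided interval. A 95% interval that excludes zero corresponds to a two-sided 5% test. The power is quoted for the easier criterion and the results will be shown on the stricter one. A reader who sees an NPI interval that includes zero would take it to come from a study with 80% power to avoid that outcome, when the figure is nearer 71%. The NPI is a primary outcome and drives the recruitment target, so this is the power statement that matters.

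**Loss.** The effect is a 12-month change, but the 20% is described as total loss, deaths included, over a two-year study. The article does not say at which time point 140 per group are expected to remain. The Background cites survival short enough to make 20% over two years look tight, and the Discussion concedes that attrition could be substantial.

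**Working it through.** **Inputs, all from the Sample size section.** Difference 5.2; SDs 13.7 and 20.3; within-subject correlation r = 0.5; 140 analysable and 175 recruited per group; one-sided α = 0.05.

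**Step 1: SD of change.** SD × √(2(1 − r)) = SD × √1, so the change SDs are 13.7 and 20.3.

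**Step 2: reproduce the plan.** Standard error at 140 per group = √(13.7²/140 + 20.3²/140) = √(599.78/140) = 2.07. Noncentrality = 5.2/2.07 = 2.51. Satterthwaite degrees of freedom are about 244.
- One-sided 5%: critical value 1.651, power 80.5%. The smallest n reaching 80% is 138 per group.
- Recruitment: 140/0.80 = 175.

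The stated figures reproduce.

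**Step 3: the criterion matching a 95% interval.** Same standard error, two-sided 5%, critical value 1.970.
- Power for 5.2 points at 140 per group: 70.6%. The chance that the 95% interval includes zero is therefore about 29%, against about 20% under the one-sided test.
- Difference detectable with 80% power at 140 per group: 5.82 points.
- Number needed for 80% power at 5.2 points: 176 analysable per group.

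This step uses no input from outside the article.

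**Step 4: what the Background's survival figures say about loss.** The assumption here is a constant hazard, which the article does not state. Two-year deaths from a median m are 1 − 2^(−2/m); from a mean μ, 1 − exp(−2/μ).

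| Figure cited in Background | Clock starts at | Deaths by 2 years |
|---|---|---|
| Median 10.7 years (age 65–69) | first symptoms | 12% |
| Mean 7 years | diagnosis | 25% |
| Median 4.6 years (women) | onset | 26% |
| Median 4.1 years (men) | onset | 29% |
| Median 3.8 years (over 90) | first symptoms | 31% |

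At 12 months, 1 − 2^(−1/m) gives 14% and 16% for the medians of 4.6 and 4.1 years.

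**Step 5: conditional power at 24 months.** Two-group t-test on completers, 175 recruited per group, difference 5.2. The loss rates are illustrative; the article gives only 20%.

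| Loss | Analysable per group | One-sided 5% | Two-sided 5% |
|---|---|---|---|
| 20% | 140 | 80.5% | 70.6% |
| 25% | 131 | 78.2% | 67.8% |
| 30% | 122.5 | 75.7% | 64.8% |
| 35% | 114 | 73.0% | 61.5% |

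**GHQ-12.** It was also sized one-sided. Its requirement rises from 21 to 27 analysable per group at the two-sided level, far below 140, so the point has no practical effect there.

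**The case against.** **The one-sided choice is disclosed and fits a directional hypothesis.** The Background expects fewer behaviour and mood problems with case management than with usual care. This is fair, and it means there is no arithmetic error. But a directional hypothesis does not turn a 95% interval into a one-sided statement, and the article announces no one-sided rule for the results. The mismatch stands. The Background's remark that "Reviews and meta-analyses of case management have yielded inconsistent results on clinical outcomes" adds little here: that sentence goes on to name caregiver burden, depression and economic outcomes, not the NPI, and says nothing of harm.

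**The survival figures do not settle the loss.** This stands. Quoting only "the estimated median survival time from dementia onset to death was 4.1 years for men and 4.6 year for women" would be selective, because the same paragraph gives figures that correspond to anything from about 12% to 31% over two years. They count from onset, first symptoms or diagnosis, not from enrolment, and terminally ill people and those expecting admission within six months are excluded. In the other direction, participants enter at any time since diagnosis, and withdrawal comes on top of death. At 12 months, 14–16% deaths leave little room for withdrawal within 20% but do not contradict it.

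**A completer t-test is not the planned analysis.** This also stands. Five assessments, regression with propensity scores and a multilevel analysis are foreseen, and people lost after an interim visit need not drop out of a repeated-measures model. If the model adjusted for baseline NPI (an assumption; the article does not say so), r = 0.5 would cut the variance from 2(1 − r) = 1 to 1 − r² = 0.75, and two-sided power at 140 would be about 82%. Matching or regional clustering could lower power. The net direction is unknown.

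**Conclusion.** The point holds as an inconsistency between the stated power and the stated form of reporting. On the plan's own inputs and its own test, a 5.2-point NPI difference has about 71% power against a 95% interval, not 80%; the 80% applies to about 5.8 points. This rests only on the declared SDs, correlation and 140 analysable per group.

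The second part is weaker. The 20% loss is described for a two-year study while the effect is a 12-month change. More than 20% loss at 24 months is plausible, given the survival figures under a constant hazard and the Discussion's own caution.

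A reader might go further and infer that the survival figures imply more than 20% loss, or that the study's real power is only 60–70%. The documents support neither. The mortality range spans 20%, the clocks do not start at enrolment, and the planned models are not a completer t-test. The 24-month powers are conditional illustrations. Nor is the sample size miscalculated: 140 and 175 are right for the test declared.

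**What to change.** Reword the NPI paragraph in the Sample size section.

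1. State the power at the two-sided 5% level that matches the 95% intervals: with 140 analysable per group, about 71% for a difference of 5.2 points, or 80% for about 5.8 points. The one-sided figure can stay beside it if labelled as such.
2. Say which time point the 20% loss refers to. Either tie it to the 12-month contrast from which the effect size comes, or add a conditional 24-month range: about 68%, 65% and 62% two-sided at 25%, 30% and 35% loss, noting that this is for a two-group t-test on completers.

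The recruitment target, design and analysis stay as they are. The cost is a few sentences and a less favourable stated power. Restoring 80% two-sided power at 5.2 points would instead take 176 analysable, or 176/0.80 = 220 recruited, per group; the fix does not ask for that.

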## Methods

### Mixed method study design

A prospective, observational, controlled, cohort design to evaluate clinical and economic effects is accompanied by a qualitative process evaluation for the study on facilitators and barriers of implementation of case management. For the controlled cohort study, dementia care-receivers and their primary informal caregiver in different case management models are compared with those from regions that do not offer case management. The participants are recruited into the study and assessed every six months for two years. The Medical Ethics Committee of the VU University medical center approved the study protocol.

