At the regional level, confounding by socio-economic differences may limit the internal validity of the comparisons. This will be corrected for by using socio-economic characteristics of the patients (e.g. education), demographic factors (e.g. age and marital status) and by checking for clustering at the regional level in the multilevel analysis. The case management models may differ in their development (some regions started case management recently while others already exist for ten years), referral modality, the case loads of case managers and their funding, causing within and across case-management model type heterogeneity, which could have an effect on the care received by the person with dementia and their carer. A description of each model will help identify differences. The risk of selection bias potentially occurs at the patient level. Firstly, there may be confounding by indication and confounding by severity of cognitive impairments, as the likelihood of referral to case-management by a general practitioner may depend on patient characteristics, such as severity of dementia. Potential confounders include demographics like age, gender, education of patients and caregivers, time in case management, dementia severity (MMSE, dementia-type and caregiver burden (Sense of Competence questionnaire [51]). Baseline characteristics of the patients in the three intervention groups will be compared and post-hoc matching techniques and stratification will be used when necessary [39]. In a secondary analysis, semi-structured interviews with a random sample of general practitioners will be performed to identify reasons for case management referral and, thus, to identify potential selection bias. Secondly, in our opinion, there is a risk of only recruiting dementia caregivers who experience relatively less burden, limiting the external validity of the study. A non-responder analysis will be completed to identify this source of potential bias and matching techniques will be used to correct for variables such as severity of cognitive impairments (MMSE), time since diagnosis and age and health of the person with dementia and caregiver.

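### The 80% NPI power assumes independent persons, although usual-care dyads are drawn from regions without case management; it is overstated for any material within-region correlation, and the effect model names no region term.

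*Protocol article*

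**What the plan says.** **Design.** Under Mixed method study design, dyads in the case management models "are compared with those from regions that do not offer case management". The abstract's Design paragraph also contrasts regions with and without case management, and the Procedure section recruits the experimental group from different regional models.

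**Sample size, NPI.** The inputs are a 12-month change of minus "2.5 (SD 13.7) in the intervention group" and "2.7 (SD 20.3) in the control group, resulting in a difference of −5.2". For the variance of change, "we assumed a within-subject correlation of 0.5 to estimate the standard deviation for the difference scores". On the test: "This calculation was based on a two group Satterthwaite *t*-test at a one sided significance of α = 0.05". The result is "A sample size of 140 participants per group is considered sufficient (80% power) to detect a difference of 5.2", and after 20% dropout "175 (140/0.80 = 175) participants per group will be recruited". No ICC, design effect or number of regions enters.

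**Analysis.** The Effect evaluation section describes intention to treat, propensity scores and regression models, with no region term. Clustering appears only in the Discussion. There, regional confounding is to be corrected using patient socio-economic and demographic characteristics and "by checking for clustering at the regional level in the multilevel analysis". The same paragraph expects heterogeneity within and across case management model types that could affect the care received.

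**The concern.** When exposure largely follows region, dyads from one region share providers, referral routes and local services. If their NPI changes are correlated, 140 people carry less information than 140 independent people, and the stated power is too high.

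The analysis text leaves a second gap. A commitment to check for clustering does not commit the authors to keep region in the model that gives the treatment effect. If region were left out, standard errors would be too small and intervals too narrow.

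The Discussion also lists the clustering check among the means of correcting regional confounding. Allowing for clustering addresses the standard error. It does not make regions with and without case management comparable.

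**Working it through.** **1. Reproduce the stated figure.** With correlation 0.5, the SD of change is SD × √(2 × (1 − 0.5)) = SD, so 13.7 and 20.3.
- Standard error at 140 per group: √((13.7² + 20.3²)/140) = √(599.78/140) = 2.070.
- 5.2/2.070 = 2.512. The Satterthwaite noncentral t at one-sided 5% gives 80.5% power (normal approximation: Φ(2.512 − 1.645) = 80.7%).
- The smallest n for 80% is 138 per group.
- 140/0.80 = 175.

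The arithmetic is correct for independent persons. The room it leaves is a design effect of 140/138 = 1.014.

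**2. Add clustering.** These inputs are assumptions: k equal regions per group, ICC 0.01 to 0.05 for NPI change, and exposure wholly between regions. With m = 140/k completers per region, the design effect is DE = 1 + (m − 1) × ICC and power is Φ(2.512/√DE − 1.645). The last column uses a noncentral t with 2k − 2 degrees of freedom instead.

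| Regions per group (m) | DE at ICC 0.01 / 0.02 / 0.05 | Power, % | Power on 2k − 2 df, % |
|---|---|---|---|
| 5 (28) | 1.27 / 1.54 / 2.35 | 72.1 / 64.8 / 49.8 | 65.2 / 58.1 / 44.2 |
| 8 (17.5) | 1.165 / 1.33 / 1.825 | 75.3 / 70.3 / 58.5 | 71.5 / 66.5 / 54.9 |
| 10 (14) | 1.13 / 1.26 / 1.65 | 76.4 / 72.4 / 62.2 | 73.5 / 69.4 / 59.4 |
| 20 (7) | 1.06 / 1.12 / 1.30 | 78.7 / 76.7 / 71.2 | 77.4 / 75.4 / 69.8 |

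Example (5 regions, ICC 0.05): the standard error becomes 2.070 × √2.35 = 3.173, and 5.2/3.173 = 1.639, giving 49.8%.

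**3. If region were left out of the model.** The true one-sided error of a nominal 5% test is 1 − Φ(1.645/√DE). With 5 regions per group it is 7.2% at ICC 0.01 and 14.2% at ICC 0.05. With 20 regions it is 5.5% to 7.5%.

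**4. The other primary outcome.** For the GHQ-12 the article uses SDs 2.8 and 3.4, correlation 0.6 and difference 2.2. The change SDs are 2.8 × √0.8 = 2.50 and 3.4 × √0.8 = 3.04, and 21 per group reproduces. At 140 per group with 5 regions and ICC 0.05, 2.2/√((2.50² + 3.04²) × 2.35/140) = 4.31, so power is above 99%.

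**The case against.** **The article does name a multilevel analysis, and model detail belongs in an analysis plan.** This stands in part. A reader might infer that the region term will be dropped after a non-significant test, or that clustering will be ignored. No passage says either, so the error rates in step 3 are conditional. Denominator degrees of freedom are commonly left to the analysis plan. What remains is that the printed text commits only to a check, and the section defining the effect model does not carry it through. The power statement is printed in full, and even a proper multilevel model would leave it overstated.

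**Patient covariates are listed too.** Correct. The article does not rely on the clustering check alone against regional confounding: it lists covariates, plans propensity scores and concedes that internal validity may be limited. The only fault is counting the check as part of the correction.

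**Exposure may vary partly within regions.** The Discussion describes referral by general practitioners depending on patient characteristics, and the usual-care definition says only that there is, as a rule, no case manager. If so, the full design effect overstates the loss.

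**The size is assumed.** Also true. The article says only that various regions in the North, West and Center are used. For change scores, stable regional differences in level cancel, so the ICC may be small. With 20 regions and ICC 0.01 the loss is slight. A reader might infer that power is near 50%. That is one corner of the range, and the documents do not establish it.

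**The arithmetic is right and the GHQ-12 is safe.** Both stand. The fault lies in the variance assumption for the NPI, the outcome that sets the 175 per group.

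**Conclusion.** The point holds for the NPI. The stated 80% requires essentially no within-region correlation, since any design effect above about 1.01 takes power below 80%. For 140 completers per group and ICC 0.01 to 0.05, power ranges from about 79% (20 regions per group, ICC 0.01) to about 50% (5 regions, ICC 0.05). With few regions it is lower still on between-region degrees of freedom. These figures assume equal regions and exposure wholly between regions, and neither the region count nor the ICC comes from the article.

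The standard-error risk follows only if region is left out of the effect model, which the text permits but does not state. The direction of the power problem is certain for any material positive ICC; its size is not. This should be corrected, but it does not invalidate the design.

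**What to change.** - **Sample size:** restate the NPI power for 140 completers (175 recruited) per group, with the actual number of regions and an ICC range such as 0.01 to 0.05. Say that the GHQ-12 is not materially affected at that size.
- **Effect evaluation:** specify that the primary models keep a region random intercept with small-sample degrees of freedom (Kenward-Roger or Satterthwaite), whatever a check for clustering shows.
- **Discussion:** state that a check or random intercept for clustering corrects standard errors, not regional confounding. Such confounding is addressed only through measured covariates and may remain.

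The cost is a less favourable stated power and wider intervals, plus a few sentences of text. No extra patients are required. The restatement discloses the power loss; it does not recover it.
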